### Sample size calculation

Each year, approximately 200 children are born before 30 weeks of gestation and admitted to the Neonatal Intensive Care Unit at the academic medical center in Rotterdam, the Netherlands. Based on previous research with this population we expect an inclusion rate of ~ 50%. Therefore, we expect to include at least 100 children at 1 year CA. There are no thorough estimates of the prevalence of VPD in preterm children. A previous study using the eye tracking-based assessment in extremely preterm children identified visual processing delays in 48% of preterm children without evidence for brain damage [16], and in 9% to 23% of children in a cross section of the preterm population at 1 year CA [15]. In addition, between 25% and 33% of children with CVI have prematurity as a contributing factor [32]. However, the prevalence of risk factors for VPD in our study population (often with brain damage and perinatal events) is much higher than 50%. Therefore, we expect that each year at least 50 newborn preterm children from the Neonatology Department (i.e., 50%) are at risk of VPD and thus eligible for inclusion in the intervention study.

### Recruitment strategies

Children will be recruited from a medical follow-up program for children born preterm that is ongoing at the Department of Neonatology. Children’s eligibility for inclusion will be screened by a multidisciplinary team (project leader and project members from Neonatology). The project leader and/or project members will approach their parents first by telephone, to ask for permission to send an information leaflet about the study. Two weeks after sending the study information, parents will be contacted again to ask for their permission to include their child in the study. The baseline assessment (i.e., the visual screening) and the 1-year follow-up assessment will be scheduled together with an existing appointment at Neonatology, to minimize burden for children and parents. Children in the control group (group 3) will be recruited through daycare centers. The parents will receive study information by mail and are asked to contact the project leader if they are willing to participate. If they give their consent, an appointment for the visual assessment will be made.

### Randomization and intervention allocation

Prior to recruitment of participants, a randomization scheme has been designed in which the order of visual intervention groups (either direct or postponed) is randomized using an online tool (Sealed Envelope Ltd. 2016; https://www.sealedenvelope.com/simple-randomiser/v1/lists).

Randomization is blocked to ensure a balance in sample size across groups over time and stratified to control and balance the influence of covariates [47]. Covariates in the current study are the presence of brain damage and gestational age (< 28 weeks or 28–30 weeks).

After this computer-generated randomization, preterm children who are classified as being at risk of VPD will be assigned a participant number and concurrently be allocated to one of the visual intervention programs. The order of allocation corresponds with the date and order of inclusion. This allocation will be done by the principal investigator and remains concealed to all other investigators, the participating children, and their parents. All participant numbers will be separately placed in opaque envelopes that contain a note with the assigned visual intervention group. Revealing the group allocation to parents will be done by opening the opaque envelopes in their presence.

### Blinding

The study set-up is single-blind. Intervention allocation will be known by the project leader managing the contacts between all involved parties, and by the behavioral therapists of the visual rehabilitation center who will perform the interventions. Parents cannot be blinded to intervention allocation either, as they will actively participate in the intervention programs. However, the allocation will be blinded for the researchers and orthoptists who perform the baseline and follow-up visual assessments, and for the researchers performing data analyses.

Prior to analyzing results of the visual intervention (i.e., analyzing results of the follow-up visual assessments), participant numbers will be converted into a new participant code and visual intervention group will be coded into a new variable (group A or B). That way, group allocation remains concealed and bias during data analysis will be prevented [48].

### Data management

All data will be handled confidentially and anonymously. Communication about participating children between the various participating departments and organizations will only be done using codes, not names or other personal identifying information. All data will be coded, and a separate coding list will link study data to personal identifying information of a specific subject. The coding list is password-protected and only accessible by the main investigator(s). Data files will be stored on a PC and will be accessible with a password that is only known to the main investigator(s). Paper documents will be stored in a locked cupboard of which only the main investigator(s) will have a key. The investigator(s) will remain blind to the participants’ outcomes during the course of the study. All data will be anonymized prior to analyses and publications. Group allocation and randomization will not be revealed until after the statistical analyses have been finished.

### Withdrawal

Parents and their children can withdraw from the study at any time for any reason if they wish to do so without any consequences. The investigator can decide to withdraw a subject from the study for urgent medical reasons. When subjects withdraw from the visual intervention program they will not be replaced in order to ensure adherence to the randomization protocol for the RCT. Withdrawal of subjects will be taken into account during data analyses by using intention-to-treat analyses. Subjects withdrawn from the visual intervention program will be followed-up with a short questionnaire (assessed by telephone) in which they are asked for their reasons and circumstances of their withdrawal.

### Statistical analyses

#### Sample size calculation

To answer our primary research question about the effectiveness of early visual intervention programs on visual attention and processing functions in preterm children at risk of VPD, we use a repeated measures analysis of variance (ANOVA) for the parameter RTF as primary analysis. An a priori power analysis provided a recommended total sample size of 32 children (and an actual power of 0.81 and a critical F of 4.17).

#### Effectiveness of visual intervention program

In children at risk of VPD who have been allocated to a visual intervention group, differences in viewing behavior parameter RTF between T0 and T1 are analyzed with a Repeated Measures ANOVA. A *p* value of 0.05 will be considered statistically significant. Covariates are the medical (perinatal and ophthalmic) and demographic factors and the repeated measures analyses will be done with and without them to obtain their contribution to the main effect. All analyses are done according to the intention-to-treat principle.

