### Participant characteristics and timeline

It is expected that 25–50% of the very preterm population is at risk of VPD at 1 year CA [15, 16]. Therefore, all infants who have been born before 30 weeks gestational age and who participate in the clinical follow-up program of the Department of Neonatology, will be available for inclusion around 1 year CA. We aim to include children from 1 year CA, born < 30 weeks of gestation (about 50% are expected to be at risk of VPD, and eligible for the intervention) (*n* = 100) and children born at term without VPD from 1 year of age, to add to an existing database of typically developing children (healthy control group) (*n* = 100). The study population will be divided into three groups, with two subgroups – Group 1: children born very preterm from 1 year CA, without a risk of VPD; Group 2: children born very preterm from 1 year CA, with a risk of VPD (50% will receive direct visual intervention (group 2A, intervention group) and 50% will receive postponed visual intervention (group 2B, control group); Group 3: children born at term without a risk of VPD.

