### Outcome measures

To answer our main research question about the effectiveness of early visual intervention in young preterm children, we will compare visual outcomes between the intervention and control group. We will analyze results from the eye tracking-based visual assessment and the additional VFAs at baseline and at yearly follow-up measurements. Primary outcomes are the changes in visual parameters after the duration of the intervention study (i.e., from baseline to follow-up T1 and/or T2), namely quantitative visual parameters (eye tracking-based visual detection and viewing reaction times) and VFA (visual acuity, contrast sensitivity, visual field, ocular motility).

Endpoints are the changes in these parameters after the visual intervention program. These parameters are chosen since their combination provides quantitative and objective results about functional viewing behavior (the eye tracking-based assessment) and clinically relevant visual function outcomes (i.e., the VFAs). In addition, we will compare the effectiveness of direct (at 1 year CA) versus postponed visual habilitation (at 2 years CA) by comparing visual outcomes between these groups at T2.

Secondary outcomes are the neurodevelopmental level at the first follow-up (T1) and results from parental questionnaires about daily visual functioning at T1 and/or T2, i.e., total score, cognitive and motor sub scores of the neurocognitive assessment with Bayley Scales of Infant and Toddler Development (Bayley-III-NL) and total score and sub scores per visual domain of the PAI-CY 0–2 Inventory (i.e., attachment, stimulus processing, orientation, play, mobility, communication). These measures were chosen because Bayley-III-NL is the only available neurocognitive assessment for children at this age, and the PAI-CY 0–2 Inventory is the only available parental questionnaire about daily (visual) behavior at this age.

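### The primary RTF analysis compares raw change and commits to neither the randomisation strata nor one decisive model; a baseline-adjusted ANCOVA would be more precise at almost no cost

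*Protocol article*

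**What the plan says.** All references are to the protocol article.

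- **Endpoint** (Outcome measures): "Primary outcomes are the changes in visual parameters after the duration of the intervention study".
- **Primary analysis** (Sample size calculation, under Statistical analyses): "we use a repeated measures analysis of variance (ANOVA) for the parameter RTF as primary analysis". The same paragraph reports a "recommended total sample size of 32 children (and an actual power of 0.81 and a critical F of 4.17". It gives no effect size, number of measurements or correlation.
- **Contrast and level** (Effectiveness of visual intervention program): "differences in viewing behavior parameter RTF between T0 and T1 are analyzed with a Repeated Measures ANOVA", and a p "value of 0.05 will be considered statistically significant".
- **Covariates in the analysis** (same section): "Covariates are the medical (perinatal and ophthalmic) and demographic factors and the repeated measures analyses will be done with and without them". The stated reason for running both is to see how much the covariates contribute to the main effect. Neither run is called primary.
- **Covariates in the allocation** (Randomization and intervention allocation): randomisation is blocked and stratified, and "Covariates in the current study are the presence of brain damage and gestational age", the latter split at 28 weeks.
- **Allocation ratio** (Participant characteristics and timeline): "50% will receive direct visual intervention (group 2A, intervention group) and 50% will receive postponed visual intervention".

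**The concern.** With two arms and two visits, the group-by-time test in a repeated measures ANOVA is the two-sample test on T1 minus T0. It subtracts the whole of the baseline value, whatever the correlation between visits. ANCOVA estimates that weight from the data, so in expectation it is at least as precise, apart from the degrees of freedom it uses. In a trial sized at 32 children the difference can matter, and T0 RTF is collected at the baseline screening in any case.

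The second part concerns the strata. The design section treats brain damage and gestational age as the influences to control. The analysis section speaks of broad classes of medical and demographic factors and does not say that these two are in the model. It then describes two runs without saying which one answers the primary question. The text therefore leaves open both whether the analysis follows the design and which estimate decides.

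**Working it through.** **Inputs from the document.** Total N = 32, power 0.81, critical F 4.17, alpha 0.05, 1:1 allocation, two visits (T0, T1). About 50 at-risk children are expected (the earlier Sample size calculation section, under Methods).

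**Input assumed.** The T0-T1 correlation r of RTF is not stated. The range shown is 0.3 to 0.9.

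**Step 1: the plan's own figure.** F(0.95; 1, 30) = 4.171, which agrees with 4.17. The 30 denominator degrees of freedom are 32 children less two groups, so the calculation had no covariates. N = 32 and power 0.81 cannot be rebuilt from the document because the effect size is missing. Two trial settings, both with assumed inputs:
- Between-group test, f = 0.40, five measurements, correlation 0.5: noncentrality 0.16 × 32 × 5 / (1 + 4 × 0.5) = 8.53, power 0.807 at N = 32.
- Two-visit interaction, f = 0.25, correlation 0.5: noncentrality 0.0625 × 32 × 2 / 0.5 = 8.0, power 0.781 at N = 32; N = 34 is needed for 0.807.

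So it is not certain that 0.81 refers to the two-visit change test. The next steps take it that way as a condition.

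**Step 2: calibrate.** Power 0.81 with F(1, 30) needs a noncentrality of 8.60. This is a standardised difference in change of √(4 × 8.60 / 32) = 1.04.

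**Step 3: relative variance.** With equal variance at T0 and T1 (set to 1):
- change: 2(1 − r)
- ANCOVA: 1 − r²
- ratio ANCOVA/change: (1 + r)/2

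With unequal standard deviations s0 and s1, change variance minus ANCOVA variance is (s0 − r·s1)², which is never negative. The direction does not depend on equal variances; the size does.

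**Step 4: power.** Divide the noncentrality by (1 + r)/2. Baseline RTF and the two strata take three degrees of freedom, leaving 27 at N = 32 and 45 at N = 50. At N = 50 the noncentrality for change is 8.60 × 50/32 = 13.44.

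| r | (1 + r)/2 | Change, N = 32 | ANCOVA, N = 32 | Change, N = 50 | ANCOVA, N = 50 |
|---|---|---|---|---|---|
| 0.3 | 0.65 | 0.81 | 0.94 | 0.95 | 0.99 |
| 0.5 | 0.75 | 0.81 | 0.90 | 0.95 | 0.99 |
| 0.7 | 0.85 | 0.81 | 0.87 | 0.95 | 0.97 |
| 0.9 | 0.95 | 0.81 | 0.83 | 0.95 | 0.96 |

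The ANCOVA columns credit the strata with no prognostic value and assume that covariates are balanced between arms. If all three covariates carried the usual cost of chance imbalance and the strata explained nothing, the N = 32 column would be 0.91, 0.87, 0.83 and 0.78. At r = 0.9 that is a small loss.

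**Step 5: simulation check.** At N = 32, with 6,000 runs per setting and change-test power set near 0.80, ANCOVA on baseline RTF alone gave 0.92, 0.88 and 0.84 at r = 0.3, 0.5 and 0.7. Adding five covariates of pure noise to the change model lowered its power from 0.80 to 0.72. A wide medical and demographic adjustment is therefore not a safe default at this size.

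**The case against.** The strongest reply is that nothing here is an error. Change-based repeated measures ANOVA on randomised arms is a valid test, and the endpoint and analysis sections agree with each other. That stands: the point concerns efficiency and an unfixed model. Entry partly on abnormal T0 RTF does not alter this, because regression to the mean is expected equally in both arms.

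Four stronger readings are tempting, and the document does not support them.

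- **The strata have been replaced by other covariates.** Gestational age is a perinatal factor and brain damage a medical one, so the broad wording can include both. What is missing is the commitment to them.
- **There are two rival primary p-values to choose from.** The stated purpose of the second run is descriptive, and the critical F of 4.17 matches a model without covariates, which hints that the unadjusted run is the one powered. Analysts also work with coded groups. In the simulation, claiming success if either run was significant gave a type I error of 0.061-0.069, but this rests on five assumed noise covariates and on a practice that the protocol does not describe. What remains is that no run is labelled as decisive.
- **The covariate list is open.** An itemised list may sit in an analysis plan that is not shown, so its absence from an article is not a fault.
- **The correlation is modest and standard errors will be too large.** The document gives no correlation. Children may also enter on a neurological risk factor alone, so selection on RTF need not be strong. Omitting strata overstates the standard error only if they are prognostic for the outcome analysed, which is not shown.

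It is also fair to say that 32 is the calculated minimum. At the 50 children expected, power for the same effect is already high.

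**Conclusion.** The point holds as a matter of efficiency and of fixing the model. The primary analysis uses raw change where a baseline-adjusted analysis of the same data would be more precise. It does not commit to the factors on which allocation was stratified, and it does not say which run decides.

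At N = 32 the gain is from 0.81 to about 0.94, 0.90 or 0.87 for r = 0.3, 0.5 or 0.7. This assumes that 0.81 belongs to the two-visit change test, that T0 and T1 variances are equal, and that r lies in that range. At about 50 children the gain is from 0.95 to about 0.97-0.99 over the same range, and it nearly disappears at either size when r is near 0.9. Any further gain from the strata depends on their being prognostic, and none is counted here. The change is worth making because it is nearly free; the planned test would not mislead if left as it is.

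**What to change.** In the section Effectiveness of visual intervention program, name one primary model: an ANCOVA of T1 RTF on arm, with T0 RTF, presence of brain damage and gestational-age stratum as the only covariates. The equivalent constrained longitudinal model would also serve. State that this model decides the primary question at 0.05. Label the unadjusted repeated measures ANOVA and the wider medical and demographic adjustment as sensitivity analyses, keeping their descriptive purpose.

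The cost is analysis wording and three degrees of freedom. No new data are needed: RTF is measured at the baseline screening, and both strata must be known in order to randomise.

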#### Other effects of visual intervention on VPD (other parameters)

Secondary study parameters are the differences in other eye tracking-based parameters of viewing behavior and the outcomes of VFAs (e.g., visual acuity, contrast sensitivity, extent of visual field). Repeated measures ANOVAs with a *P* value of 0.05 will be considered statistically significant. After finding a main effect of group on the viewing behavior parameters, post-hoc comparisons will be done to establish which of the five visual stimuli significantly differ from each other in parameter values. For these comparisons, Bonferroni’s correction will be applied to the viewing behavior variables to correct the *P* value for the number of comparisons.

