#### Follow-up after 1 year

One year after inclusion, the children at risk of VPD will repeat the visual function assessments, and all included children (with and without VPD risk) will repeat the eye tracking-based visual screening and undergo a neurodevelopmental assessment (that is standard care at most Neonatology departments, from 2 years CA). That way, the specific effects of early visual intervention on visual processing and neurocognitive development are compared and evaluated.

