#### Effects of visual intervention on neurodevelopment

At 2 years of age, parameters from Bayley-III-NL are used as indicators of neurocognitive development. First, the relation between the visual assessment parameters and Bayley-III-NL parameters of the cognitive composite score, the language composite score, and the motor composite score will be analyzed using Pearson and Spearman correlation analyses. Next, univariate ANOVA’s are used to analyze differences in Bayley-III-NL scores between preterm children without a risk of VPD and children at risk of VPD, and between preterm children at risk of VPD in the direct versus the postponed intervention group.

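### Each visual outcome other than RTF is tested at an unadjusted 0.05, with no correction across outcomes and no exploratory label, although Outcome measures lists these outcomes as primary

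*Protocol article*

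**What the plan says.** All references are to the protocol article.

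- **Primary analysis.** Under Statistical analyses, Sample size calculation, a repeated measures ANOVA is planned "for the parameter RTF as primary analysis". The next section, Effectiveness of visual intervention program, takes the change from T0 to T1 and sets the level: a p "value of 0.05 will be considered statistically significant. Covariates are the medical (perinatal and ophthalmic) and demographic factors".
- **Other visual outcomes.** The section Other effects of visual intervention on VPD (other parameters) calls the remaining eye-tracking parameters and the VFA outcomes secondary. It says of their repeated measures ANOVAs that a P "value of 0.05 will be considered statistically significant. After finding a main effect of group on the viewing behavior parameters", and goes on to post-hoc comparisons among the five stimuli. For those comparisons, Bonferroni's correction "will be applied to the viewing behavior variables to correct the" P value.
- **Status elsewhere.** Outcome measures places visual detection, viewing reaction times and four VFA outcomes (acuity, contrast sensitivity, visual field, ocular motility) together under primary outcomes.
- **Non-visual outcomes.** Effects of visual intervention on neurodevelopment plans ANOVAs of Bayley-III-NL scores, among them "between preterm children at risk of VPD in the direct versus the postponed intervention group", without a significance level. Outcome measures lists as secondary the "total score and sub scores per visual domain of the PAI-CY 0–2 Inventory", but the statistical section describes no test for them.

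**The concern.** The article states a decision rule here; it does not leave the matter open. Multiplicity was considered, but only one level down: among stimuli, once an outcome already shows a group effect. Whether an outcome shows that effect is decided by its own test at a full 0.05, and there are several such outcomes. None of these tests depends on the RTF result, shares alpha with another, or is labelled exploratory.

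If the program does nothing, the chance that some visual outcome other than RTF comes out significant is therefore well above 0.05. That would matter less if these outcomes were clearly supportive, but Outcome measures puts them among the primary ones. A chance result on acuity or detection could then be presented as a main finding of what the article describes as the first randomized trial of visual intervention at this age.

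**Working it through.** **Step 1: the plan's own figure.** The only stated figure that reflects alpha is in the power statement: "recommended total sample size of 32 children (and an actual power of 0.81 and a critical F of 4.17". With two groups and 32 children, the error degrees of freedom are 32 − 2 = 30. The 95% point of F(1, 30) is 4.171, which matches 4.17. The RTF test therefore uses the whole 0.05, and nothing is held back for other outcomes. The power of 0.81 cannot be checked because no effect size is given, and this point does not need it.

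**Step 2: what the gate and Bonferroni cover.**
- *Between outcomes:* one ANOVA per outcome at 0.05, with no adjustment and no order.
- *Within the viewing behavior variables:* stimulus comparisons only after a group effect, with Bonferroni.

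The second level cannot reduce false positives at the first, because it begins only after the first has been declared significant.

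**Step 3: number of tests (assumed).** Detection plus acuity, contrast sensitivity, visual field and ocular motility gives k = 5. The section on other effects names only the first three VFA outcomes, as examples. Motility comes from the list in Outcome measures. Without it, k = 4.

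**Step 4: chance of at least one false positive when the program has no effect.** For independent tests, each at exactly 0.05, the chance is 1 − 0.95^k:

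- k = 4: 1 − 0.95^4 = 0.185
- k = 5: 1 − 0.95^5 = 0.226

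For correlated tests, equicorrelated standard normal statistics were simulated (400,000 draws), counting draws in which any absolute value exceeded 1.96. For k = 5:

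| Pairwise correlation | 0 | 0.3 | 0.5 | 0.8 |
|---|---|---|---|---|
| At least one false positive | 0.226 | 0.208 | 0.183 | 0.127 |

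Relative to 0.05 this is 0.127 / 0.05 = 2.5 times to 0.226 / 0.05 = 4.5 times.

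**Step 5: comparison.** Bonferroni across the five outcomes (0.01 each) would give 1 − 0.99^5 = 0.049 for independent tests.

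**Step 6: if Outcome measures governs.** RTF then joins the other five as co-primary, all at 0.05. For independent tests, 1 − 0.95^6 = 0.265.

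**The case against.** The strongest defence is that unadjusted 0.05 tests of outcomes labelled secondary, beside one named primary analysis, are common practice, and readers know to discount them. The error rate of the RTF test is not touched. The Discussion ties clinical implementation to achieving the study goals, not to an isolated p value. All of this stands, and it limits the weight of the point. It does not remove it, because the label is not consistent: the analysis section calls these outcomes secondary and Outcome measures calls them primary.

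A reader might also infer something stronger: that every secondary comparison, including Bayley-III-NL and PAI-CY, is declared significant at 0.05, so that a false claim somewhere is likely. The article does not support that.

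- The 0.05 threshold is attached only to the repeated measures ANOVAs on visual parameters. No level is given for Bayley-III-NL and no test for PAI-CY, and silence that an analysis plan may fill is not a fixed rule.
- Larger counts are therefore illustrative only. At correlation 0.5 (range for 0.8 to 0), adding three Bayley composites (8 tests) gives 0.25 (0.16 to 0.34). Adding the PAI-CY total and six listed domains (15 tests) gives 0.36 (0.20 to 0.54). Repeating the visual and PAI-CY outcomes at T2 (27 tests) gives 0.49 (0.25 to 0.75). The last figure also assumes separate tests at T2, whereas one repeated measures ANOVA can take several visits.
- Even so, no figure at correlation 0.5 reaches one half. With independent tests it takes 14 (1 − 0.95^14 = 0.512), and a questionnaire total is not independent of its own sub scores.
- The statement under Follow-up after 1 year that "the specific effects of early visual intervention on visual processing and neurocognitive development are compared and evaluated" describes what the follow-up is for. It is not a rule for claiming effects.

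**Conclusion.** The point holds for the visual outcomes other than RTF. Their ANOVAs are each declared significant at an unadjusted 0.05, and the existing gate and Bonferroni correction do not work across outcomes. With about five tests, the chance of at least one false positive under no effect is about 0.18, with a range of 0.13 to 0.23.

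This rests on an assumed count of five, assumed equal correlations between 0 and 0.8, each test holding its nominal level, and no effect on any of the outcomes. In roughly four trials out of five or more, no such false positive would occur, so the risk is material but not likely to be realised in any one trial.

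The weight is moderate: the RTF conclusion is safe, but the conflicting status of the other visual outcomes leaves room to present a chance result as a main one. The point does not extend, as something the article fixes, to Bayley-III-NL or PAI-CY.

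**What to change.** In Other effects of visual intervention on VPD (other parameters), replace the 0.05 rule with wording to this effect, in line with the primary analysis already named: *The change in RTF from T0 to T1 is the only confirmatory test, at 0.05. Comparisons of the other eye-tracking parameters and of the VFA outcomes are exploratory; they are reported as estimates with 95% confidence intervals and carry no claim of significance.*

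Then bring the primary-outcome wording of Outcome measures into line, so that detection and the VFA outcomes have the same status in both places, and give the Bayley-III-NL and PAI-CY comparisons that status too. A short set of secondary outcomes tested with Holm's procedure after a significant RTF result would be an acceptable alternative, but it is a matter of preference and not required.

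The cost is wording in the outcome and analysis sections, with no change to data, participants or procedures. The downside is that an isolated p value below 0.05 on one of these outcomes can no longer be claimed as a proven effect, and that detection and the VFA outcomes give up the primary status that Outcome measures now gives them.

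### The post-hoc tests compare the five visual stimuli with one another instead of comparing the arms on each stimulus, and the group main effect that precedes them is the right test only under a model the protocol does not state

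*Protocol article*

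**What the plan says.** Under Outcome measures, the protocol article sets out the question: "we will compare visual outcomes between the intervention and control group". It defines the primary outcomes as changes from baseline to follow-up at T1 and/or T2.

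Under Effectiveness of visual intervention program, the analysis for reaction time to fixation (RTF) is given as "differences in viewing behavior parameter RTF between T0 and T1 are analyzed with a Repeated Measures ANOVA". Covariates are to be added and removed "to obtain their contribution to the main effect". The factor to which that main effect belongs is not named.

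Under Other effects of visual intervention on VPD (other parameters), repeated measures ANOVAs are planned for the remaining eye-tracking parameters and the visual function assessments. For the viewing behavior parameters the text continues: "After finding a main effect of group on the viewing behavior parameters, post-hoc comparisons will be done". Their stated purpose is "to establish which of the five visual stimuli significantly differ from each other in parameter values", with a Bonferroni correction for a number of comparisons that is not given.

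No section names a group-by-time term, a between-arm test of change, a T1 comparison adjusted for T0, or a comparison of the direct and postponed arms within a stimulus.

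**The concern.** The trial asks whether early intervention improves visual processing more than placebo support does. The Discussion puts the difficulty itself: is an improvement due to the intervention or to normal development? Only a between-arm contrast of change, or of T1 given T0, separates the two.

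The post-hoc step asks something else. Finding that reaction times to one kind of stimulus are longer than to another describes the stimuli or the children, not the intervention. The supplement protocol is tailored to the functions in which a child is deficient, with form and motion as the article's example, so the effect by stimulus is a natural thing to want. As written, no test supplies it.

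The step is also conditional on a group main effect. Depending on what enters the ANOVA, that is either the correct test or a diluted one. In the second case, a real effect on these parameters could fail to open the step.

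**Working it through.** **1. The post-hoc contrast (no assumptions needed).** Set the two questions side by side.

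- Wanted: for each of the five stimuli, is the T0–T1 change different in the direct and postponed arms? That is 5 contrasts; Bonferroni 0.05/5 = 0.01 each.
- Stated: do the stimuli differ from one another? If all pairs are compared, that is 5 × 4/2 = 10 contrasts; Bonferroni 0.05/10 = 0.005 each. The count of 10 is an inference, because the protocol gives none.

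If the stimuli are compared after pooling the arms, the arm difference drops out. If they are compared within the direct arm, even on change scores, maturation stays in and there is no control. Neither shows where the arms differ.

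**2. The plan's own figures.** The Statistical analyses section gives N = 32, power 0.81 and critical F 4.17. With two groups, the 95th percentile of F on 1 and 30 df is 4.171, which reproduces 4.17. Power 0.81 then needs a noncentrality λ of about 8.60. The effect size f, the correlation and the number of measurements are not stated, so N and power cannot be derived from the document. Several input sets fit, for example:

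- Group main effect over m = 5 measures, assumed f = 0.40 and ρ = 0.5: λ = f²Nm/(1 + (m−1)ρ) = 0.16 × 32 × 5/3 = 8.53, power 0.807.
- Group-by-time with m = 2, assumed f = 0.20 and ρ = 0.7: λ = f²Nm/(1−ρ) = 0.04 × 32 × 2/0.3 = 8.53, power 0.807.

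The power figure therefore does not reveal which effect was meant.

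**3. The group main effect if raw T0 and T1 values are analysed.** Screening precedes allocation, so the expected arm difference at T0 is zero. Let the T1 difference be d (SD units), the T0–T1 correlation r, and allocation 1:1.

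- The group main effect estimates (0 + d)/2 = d/2, with λ_main = Nd²/(8(1+r)).
- Group-by-time estimates d, with λ_int = Nd²/(8(1−r)).
- Ratio: λ_main/λ_int = (1−r)/(1+r).

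Fix λ_int at 8.60 (power 0.81, N = 32, 1 and 30 df). This attaches the 0.81 to group-by-time as an assumption, to give a scale. The protocol gives no r, so a range is shown.

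| r (assumed) | (1−r)/(1+r) | λ_main | Power, group main effect |
|---|---|---|---|
| 0 | 1.00 | 8.60 | 0.81 |
| 0.1 | 0.82 | 7.04 | 0.73 |
| 0.2 | 0.67 | 5.73 | 0.64 |
| 0.3 | 0.54 | 4.63 | 0.55 |
| 0.5 | 0.33 | 2.87 | 0.37 |
| 0.7 | 0.18 | 1.52 | 0.22 |

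Simulation with 20,000 runs gave main-effect power 0.81, 0.37 and 0.22 at r = 0, 0.5 and 0.7, in agreement. At r = 0 no power is lost, although the estimate is still half the T1 difference.

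**4. The group main effect if change scores are analysed.** With T1 − T0 as the response and stimulus as the repeated factor, the group main effect is the between-arm difference in change averaged over stimuli. Nothing is diluted.

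**The case against.** The strongest reply is that the ANOVA may be on change scores. The endpoints are defined as changes, the RTF analysis speaks of differences between T0 and T1, and a five-measure group main effect with f = 0.40 and ρ = 0.5 fits the stated sample size. On that model the group main effect is exactly right. This stands as a possibility. It is not proof, because other inputs fit equally well and the article states neither model. It also does not rescue the post-hoc contrast.

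A second reply is that the authors surely meant the stimuli on which the groups differ. Perhaps so, but the sentence says the stimuli differ from each other, and an analyst following it would run a different test.

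A third is that a condensed article may leave model terms to an analysis plan. That is fair for the RTF analysis, where a term is merely unnamed. It does not cover the post-hoc step, where a specific contrast is stated and a later plan would have to contradict it.

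Two stronger readings are tempting and should not be drawn. One might infer that the primary RTF test is a pooled before–after comparison confounded with maturation. The text does not say so: it names no factor, and Outcome measures states a between-arm comparison. One might also infer that the trial as a whole would often miss a real effect. The group-main-effect condition is written only for the viewing behavior parameters in the secondary section and governs only the post-hoc step. The primary RTF analysis and the Bayley comparison do not pass through it.

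**Conclusion.** The post-hoc contrast is wrong for the trial's question whichever way the ANOVA is built, and this conclusion rests on no assumed number. The group main effect is a conditional fault. On raw T0 and T1 values it estimates half the T1 difference, and its power falls from 0.81 at r = 0 to 0.22 at r = 0.7, given 0.81 for group-by-time at N = 32. On change scores with stimulus as the repeated factor it is correct. The protocol does not say which applies. The correlation, and the attachment of the 0.81 to group-by-time, are assumptions.

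Severity: should be fixed. The explicit fault is confined to the secondary and post-hoc analysis; for the primary RTF analysis the point is only that the tested effect should be named.

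**What to change.** In Other effects of visual intervention on VPD (other parameters):

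- Replace the group main effect with the between-arm difference in T0–T1 change, as the group-by-time term or as T1 adjusted for T0. If change scores with stimulus as the repeated factor were intended, state that model; the group main effect may then stay.
- Replace the post-hoc sentence with, for example: *The difference between the direct and postponed arms in T0–T1 change (or in T1 adjusted for T0) will be estimated for each of the five stimuli and tested at 0.01, a Bonferroni correction for five comparisons.*

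In Effectiveness of visual intervention program, name the same between-arm effect as the test for RTF.

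The cost is wording only, with the same data, sample and software. The change should be made and dated before group allocation is revealed.
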